# Rationale, design, and methods of electroencephalography-based investigation of the effects of oral desmopressin on improving slow-wave sleep time in nocturnal polyuria patients (the DISTINCT study): protocol for a single-arm, open-label, single-assignment trial

**DOI:** 10.1186/s12894-020-00668-5

**Published:** 2020-07-11

**Keywords:** Nocturia, Nocturnal polyuria, Desmopressin, Sleep quality, Slow-wave sleep, Delta power

## Abstract

**Background:**

Nocturia is one of the most bothersome lower urinary tract symptoms and often impairs sleep quality in the elderly. Although previous studies on nocturia have indicated that the successful treatment of nocturia improves sleep quality, most used questionnaires and activity devices to analyze sleep/wake patterns. Therefore, there is little information about the treatment effects of desmopressin on objective sleep quality. The aim of the DISTINCT study is to investigate the change in subjective and objective sleep quality using electroencephalography (EEG) and the Pittsburgh Sleep Quality Index (PSQI) after the administration of desmopressin in patients with nocturia due to nocturnal polyuria.

**Methods:**

A total of 20 male patients, ≥65 years old, with nocturnal polyuria, defined as a nocturnal polyuria index (NPi) (nocturnal urine volume / 24 h urine volume) value ≥0.33, will participate in this study. The participants must have a nocturnal frequency of ≥2 and the first uninterrupted sleep period (FUSP) must occur within < 2.5 h. Desmopressin 50 μg per day will be orally administered before going to bed for 4 weeks. Urinary frequency volume charts (FVC) and EEG will be recorded prior to treatment and at 1 week and 4 weeks after the initiation of treatment. The PSQI will be completed before and 4 weeks after treatment. The primary endpoint is the change from baseline in the mean time of slow-wave sleep (sleep stages N3 and N4) at 4 weeks. The secondary endpoints include the change in the mean value of each sleep variable, the mean delta power during the FUSP, the correlation between nocturnal urinary frequency and slow-wave sleep time, and the change in PSQI score before and after treatment.

**Discussion:**

The DISTINCT study will provide valuable evidence to indicate that oral desmopressin treatment for nocturnal polyuria prolongs the FUSP, resulting in the extension of slow-wave sleep time associated with sleep quality.

**Trial registration:**

The Japan Registry of Clinical Trials (jRCTs051190080). Registered 9 December, 2019.

## Background

Nocturia is a common disease in the elderly. One consequence of nocturia is the complaint of poor sleep quality due to polyuria and nocturnal voids [1]. Nocturia is defined by the International Continence Society as “The number of times urine is passed during the main sleep period. Having woken to pass urine for the first time, each urination must be followed by sleep or the intention to sleep” [2]. The prevalence of nocturnal urinary frequency ≥ 2 is 47% in Japanese residents ≥65 years old [3], 36% in European residents from 60 to 80 years old [4], and 14.2% in the United States (mean age of patients is 46 years) [5]. Nocturia correlates with age, race/ethnicity, medical problems (such as hypertension, diabetes, and stroke), psychological aspects, tasting habits, quality of life, and even mortality [6].

Nocturia causes poor sleep quality by prompting nocturnal voids during the first uninterrupted sleep period (FUSP) [7, 8]. Nocturia increases the number of nocturnal voids, and nocturnal voiding has been shown to be an independent predictor of both self-reported insomnia (75% increased risk) and reduced sleep quality (71% increased risk), along with female gender and other medical psychiatric conditions [7]. Nocturia decreases the FUSP, and the FUSP is a potentially valuable metric that correlates with changes in perceived sleep duration, depth, quality of sleep for the entire night, efficiency, and latency, as evaluated by Pittsburgh Sleep Quality Index (PSQI) [8]. The FUSP has a close relationship with slow-wave, or non-REM, sleep. Sleep stages are divided from 1 to 4, and slow-wave sleep occurs during stages N3 and N4. Stages N3 and N4 commonly occur during the first two sleep cycles (about 180 min after falling asleep) and are considered important for high-quality sleep [9].

We hypothesize that desmopressin treatment for nocturia will improve subjective and objective sleep quality. Desmopressin 25 and 50 μg orally disintegrating tablets are now available worldwide for nocturia and have been shown to decrease the number of nocturnal voids [10]. It is reported that subjective sleep quality, estimated by a quality of life questionnaire, was improved by desmopressin treatment [11]. Desmopressin prolonged the FUSP, suggesting that the slow-wave sleep time might also have been prolonged, although this has not been investigated.

The aim of the DISTINCT study is to use electroencephalography (EEG) and PSQI to investigate the change in subjective and objective sleep quality after the administration of desmopressin to patients with nocturia due to nocturnal polyuria.

## Methods/design

This is a single-arm, open-label, single-assignment study. It is an exploratory study to compare subjective and objective sleep qualities after 1 week and 4 weeks of desmopressin treatment for nocturnal polyuria (Fig. 1). Qualifying patients will be males, ≥65 years old, and suffering from insomnia due to nocturnal polyuria, defined as a nocturnal polyuria index (NPi) value (nocturnal urine volume / 24 h urine volume) of ≥0.33 [2].

**Fig. 1 Fig1:**
[figure not shown]
Study design. A total of 20 patients with nocturnal polyuria will participate in this study. After the conformation of eligibility, the enrolled patients will be treated with oral desmopressin 50 μg per day. In the pre-screening period, 2-day frequency volume chart (FVC) and sleep encephalography (EEG) will be recorded and the Pittsburgh Sleep Questionnaire Index (PSQI) will be completed. Before visit Day 0, 2-day FVC and EEG will be recorded. Before visit Day 7 and Day 28, 2-day FVC and EEG will be recorded. On visit Day 28, the PSQI will be completed

This study will be conducted at Nara Medical University Hospital in compliance with both the articles of the Declaration of Helsinki (revised in October 2013) and the Ethical Guidelines for Medical and Health Research Involving Human Subjects established by the Ministry of Health, Labor, and Welfare in Japan.

### Planned outcomes

#### Primary endpoint

The primary endpoint is the change in mean time of slow-wave sleep (stages N3 and N4) as evaluated by EEG at 28 days from baseline (Table 1).

**Table 1 Tab1:** Primary and secondary endpoints of the DISTINCT Study

Primary endpoint	Secondary endpoints
Change in mean time of slow-wave sleep (N3 + N4) as evaluated by EEG at 28 days from baseline	1. Change is PSQI before and after desmopressin administration
	2. Change in nocturnal urinary frequency, the first nocturnal urinary volume, and the FUSP before and after desmopressin administration
	3. Change in sleep time, sleep effiency, and sleep quality as estimated by VAS before and after desmopressin administration
	4. Correlation between slow-wave sleep time (N3 + N4) and PSQI, VAS, FUSP, nocturnal urinay frequency at 28 days from baseline
	5. Change is delta power during the FUSP before and after desmopressin administration

*N1–4* non-rapid eye movement sleep stage 1–4, *EEG* eletroecephalography, *PSQI* Pittsburgh sleep quality index, *FUSP* the first uninterrupted sleep period, *VAS* visual analogue scale

#### Secondary endpoints

The secondary endpoints are listed in Table 1.

##### Safety endpoints

Data on the clinical trial results, vital sign measurements, and adverse events (AEs), especially signs of hyponatremia, will be collected at each visit. The severity, causal relationship to desmopressin, and outcomes of all AEs will be assessed.

### Study population

A total of 20 male patients, ≥65 years old, with nocturnal polyuria, will participate in this study. The participants must have nocturnal frequency ≥ 2 and NPi ≥0.33, which will be recorded by 2-days FVC. Patients will be considered eligible for the study if they fulfill all of the inclusion criteria and none of the exclusion criteria, as defined in Table 2. The investigator will provide a sufficient explanation of the study to each patient and obtain written informed consent prior to the initiation of any study procedures.

**Table 2 Tab2:** Inclusion and exclusion criteria of the DISTINCT Study

Inclusion criteria	Exclusion criteria
1. Nocturnal urinary frequency is 2 or more.	1. Concentration of serum sodium is less than 135 mEq/L
2. Nocturnal polyuria index is 0.33 or more.	2. Habitual or psychogenic polydipsia
3. FUSP is 2.5 h or less.	3. Heart failure, the history of heart failure, or suspected heart failure
4. Concentration of serum sodium is 135 mEq/L or more.	4. Fluid retention that requires diuretic treatment, whether currently or in the patient’s medical history
5. Creatinine clearance or eGFR is 50 mL/min/1.73m^2^ or more.	5. Antidiuretic hormone incompatible secretion syndrome
6. Patients with BPH or OAB are acceptable if the storage symptoms (urgency and daytime frequency) are well managed and stable for 3 months or more by any treatments or 6 months or more by 5-alpha reductase inhibitors.	6. Moderate or severe renal failure (Creatinine clearance or eGFR < 50 mL/min/1.73m^2^)
	7. Hypersensitivity to desmopressin or the history, whether currently or in the patient’s medical history
	8. Concomitant or scheduled administration of thiazides, thiazide-like diuretics, or loop diuretics
	9. Concomitant or scheduled administration of corticosteroids
	10. Cardiac pacemaker implantation
	11. Judged to be inappropriate by the principal investigator or subinvestigators

*FUSP* the first uninterrupted sleep period, *BPH* benign prostatic hyperplasia, *OAB* overactive bladder, *eGFR* estimate glomerular filtration rate

### Treatment

Patients will be provided with desmopressin 50 μg (as MINIRINMELT® OD Tablets 25 μg / 50 μg; Ferring Pharmaceuticals Co., Ltd., Tokyo, Japan) to be orally administered once daily prior to going to bed. The drug has been approved only for male patients with nocturnal polyuria in Japan.

### Measurements

The schedule of data collection is detailed in Table 3. A window of ±2 days is acceptable.

**Table 3 Tab3:** Schedule of enrollment, interventions, and assessments

	Study period								
	Pre-screening		Treatment						
**Timepoint:**	Visit 1	Visit 2	Visit 3			Visit 4			Visit 5
	Day −28 to −14	Day −14 to − 1	Day 0	Day 5	Day 6	Day 7	Day 26	Day 27	Day 28
**Enrollment:**									
Eligibility screen	X								
Informed concent	X								
Registration		X							
**Intervention:**									
Desmopressin									
**Assessment:**									
Patient characteristcs	X								
Blood test	X	X				X			X
PSQI		X							X
EEG		X		X	X		X	X	
VAS			X			X			X
FVC		X		X	X		X	X	
Checking for AEs						X			X

*AEs* adverse events

#### Informed consent and registration

The principal investigator or co-investigator will explain the study to each eligible participant, using the informed consent documents. Participants who give written informed consent will be registered in this study. Registration will be closed when the planned total number of participants (20 participants) is reached.

#### Data collection

Patient characteristics will include age, height, weight, and medical history. Blood tests performed at pre-screening will evaluate the following clinical chemistry analytes: serum creatinine, estimated glomerular filtration rate, sodium (Na), potassium, chlorine (Cl), brain natriuretic peptide, fasting blood glucose, white blood cell count, red blood cell count, hemoglobin content, hematocrit, platelet count, total protein, albumin, blood urea nitrogen, aspartate aminotransferase, alanine aminotransferase, alkaline phosphatase, and gamma-glutamyl transferase. Blood tests performed during the treatment period will evaluate Na and Cl.

A mobile EEG device, Sleep Graph® (Proassist, Ltd., Osaka, Japan), will be used for EEG recordings. The device is small, easy to carry, and well-validated by standard methods (polysomnography) [12]. The device records brain-waves during sleep, which indicate sleep stages.

The FVC will be recorded by the patients independently to assess the nocturnal frequency and nocturnal urine volume. The results of the visual analog scale (VAS) will be used as additional indicators of subjective sleep quality on days when FVC and EEG are recorded. The VAS is a measurement instrument that asks patients to rate their sleep from “I could sleep well” (left end of the scale) to “I could not sleep at all” (right end of the scale). Subjective sleep quality will be assessed by the length between the left end and the point at which a patient records their sleep rating.

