#### Secondary endpoints

A Wilcoxon matched-pairs signed rank test will be used to compare the mean score of the PSQI at Day 28 with that at baseline, and the mean time of slow-wave sleep (N3 + N4) at Day 5 or 6 with that at baseline. Friedman’s test and Dunn’s multiple comparisons test will be used to compare the change in mean total sleep time, mean sleep efficiency, mean sleep latency, mean VAS, mean time of sleep stages, and delta power during the FUSP from baseline to Day 26 or 27. The dependency between the mean time of slow-wave sleep (N3 + N4), the score of the PSQI, VAS, FUSP, number of voids, delta power during the FUSP, and other baseline characteristics will be analyzed using a linear regression model at Day 28. The significance level for statistical tests will be 0.05 on two sides.

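### The sleep VAS is scheduled on days that share no column with the EEG and FVC recordings, while the text ties it to those recordings and analyses it at Day 26 or 27

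*Protocol article*

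**What the plan says.** All references are to the protocol article.

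- **Data collection:** VAS results "will be used as additional indicators of subjective sleep quality on days when FVC and EEG are recorded". The patient rates his sleep on a line. No recall period is given.
- **Table 3:** the VAS is marked at Day 0, Day 7 and Day 28. EEG and FVC are marked at Visit 2 (Day −14 to −1) and on Days 5, 6, 26 and 27.
- **Statistical analysis, Secondary endpoints:** the variables for the Friedman and Dunn tests include "mean VAS, mean time of sleep stages, and delta power during the FUSP from baseline to Day 26 or 27". The regression linking slow-wave sleep time with VAS and other variables "will be analyzed using a linear regression model at Day 28".
- **Table 1:** secondary endpoint 3 includes "sleep quality as estimated by VAS before and after desmopressin administration", with no study day named. Secondary endpoint 4 correlates slow-wave sleep time with "PSQI, VAS, FUSP, nocturnal urinay frequency at 28 days from baseline".
- **Fig. 1 legend:** two-day FVC and EEG recordings precede the Day 0, Day 7 and Day 28 visits. The legend does not mention the VAS.

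**The concern.** A sleep VAS is a rating of some particular night or nights. Secondary endpoint 4 sets it against EEG slow-wave sleep, so the comparison is clean only if both describe the same nights. Data collection appears to intend this; Table 3 does not deliver it. A site following Table 3 collects the rating at the clinic visit. A site following the text collects it with the home recordings. The analyst is told to use a value for Day 26 or 27 that the schedule does not produce.

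The VAS is also the only subjective measure scheduled at all three time points, since the PSQI is completed only at Visit 2 and Day 28. If sites differ, or if the baseline rating refers to other nights than the baseline EEG, the subjective–objective comparison becomes noisier. A same-night rating that was not collected cannot be recovered later.

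**Working it through.** **1. Schedule, read column by column from Table 3**

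| Column | EEG | FVC | VAS |
|---|---|---|---|
| Visit 1, Day −28 to −14 | – | – | – |
| Visit 2, Day −14 to −1 | X | X | – |
| Day 0 | – | – | X |
| Day 5 | X | X | – |
| Day 6 | X | X | – |
| Day 7 | – | – | X |
| Day 26 | X | X | – |
| Day 27 | X | X | – |
| Day 28 | – | – | X |

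EEG and FVC occupy five columns and the VAS three; none is shared. A shift in text extraction is an unlikely cause: the VAS marks at Days 7 and 28 fall in the same columns as the blood test and the adverse-event check.

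**2. Each planned use of the VAS against that schedule**

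| Use | Time point named | VAS in Table 3? |
|---|---|---|
| Data collection text | EEG/FVC days | No, on none of them |
| Friedman and Dunn tests | Baseline to Day 26 or 27 | Not on Day 26 or 27; nearest is Day 28 |
| Endpoint 3, change in VAS | Before and after | Yes, Day 0 and Day 28 |
| Endpoint 4 and regression | Day 28 | Yes, but the EEG partner comes from Days 26 and 27 |

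The first two uses conflict with Table 3. The last two can be formed.

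**3. Which night a visit-day rating describes.** This is an assumption, because the article does not say. If the rating covers the night just ended, and an EEG day labels the night that begins on it, the Day 7 rating matches the Day 6 recording and the Day 28 rating the Day 27 recording. Days 5 and 26 have no rating. If the label means the night that ends on that day, neither visit rating matches a recorded night.

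**4. Baseline.** Visit 2 spans Day −14 to Day −1 and the rating is on Day 0. The EEG therefore precedes the rating by between 0 − (−1) = 1 day and 0 − (−14) = 14 days. Fig. 1 places a recording before the Day 0 visit but does not say how long before.

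**5. The ±2-day window.** If it applies separately to each assessment, the Day 27 recording can fall on Days 25 to 29 and the Day 28 rating on Days 26 to 30. The rating then lies between 26 − 29 = −3 and 30 − 25 = 5 days after the recording. The window can close the gap or widen it.

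**6. Precision of one rating against two.** The article gives no VAS variance. Let s be the between-patient variance of true change and e the variance of a single night's rating, with nights independent. The SD of change is √(s + 2e) with one rating per time point and √(s + e) with two, so the ratio is √((s + 2e)/(s + e)). It is 1.00 when e = 0, √(4/3) = 1.15 when s = 2e, √(3/2) = 1.22 when s = e, and √2 = 1.41 when s = 0. The increase is anywhere from 0 to 41%.

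**7. Sample size.** The stated 13 reproduces without the VAS. With 33.2 min, SD 35.7 min and two-sided 5%, a paired t-test needs 12; dividing by the Wilcoxon efficiency 0.955 gives 12.57, hence 13. Simulated signed-rank power is 79.4% at 12 and 85.0% at 13.

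**The case against.** The strongest reply is that the passages describe one design loosely. Fig. 1 puts each two-day recording just before a visit, so a visit-day VAS may be meant to cover the recording just completed. The Data collection sentence says how VAS results will be used, not outright that the form is filled in on those days. Day 28 also seems to serve as a general label for week 4, because the regression at Day 28 uses EEG data from Days 26 and 27. On that reading the follow-up time points can be reconciled.

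This is plausible, but the article does not state it. It still leaves one mark on the line for two nights, and the interval between baseline EEG and Day 0 remains open.

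Other parts of the reply stand, and they rule out three stronger readings that a reader might infer:

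- **That the VAS endpoints cannot be formed.** They can. Days 0, 7 and 28 support a before/after change, a three-time-point Friedman test and a Day 28 regression.
- **That the study aim is undermined.** The Discussion rests the aim on PSQI and EEG. The VAS is an additional indicator in a study described as exploratory. The baseline gap also does not enter a Day 28 regression, nor does a change in VAS alone need a same-night EEG.
- **That a known amount of precision is lost.** Mean VAS may be a group mean: the same section speaks of a mean PSQI score, and the PSQI is taken once per time point. No two-night average is specified, and a single figure such as 22% depends on an assumed variance split.

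**Conclusion.** The inconsistency is real and moderate in weight. As written, Table 3, Data collection and the secondary analysis cannot all be followed: the VAS and EEG/FVC columns do not overlap at all, and no VAS is scheduled on Day 26 or 27. The VAS endpoints remain computable from the Table 3 days, but not in the way the two text sections describe, and nothing ensures that a rating refers to recorded nights. The loosest point is baseline, where the separation can reach 14 days under Table 3 taken at face value, without the ±2-day window.

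The effect is confined to secondary endpoints 3 and 4. The primary endpoint, its test and the sample size of 13 (20 enrolled) do not depend on it. The schedule conflict needs no outside figure. The statement about which nights match depends on the recall period and the meaning of the day labels, and the article gives neither. The precision loss should be quoted, if at all, only as an assumption-dependent range of 0 to 41%.

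**What to change.** 1. **Table 3:** mark the VAS for the morning after each EEG/FVC night, that is the baseline recording nights and the nights of Days 5, 6, 26 and 27. Put the line in the home diary with the FVC.
2. **Data collection:** state that each rating refers to the night just ended and is completed the next morning.
3. **Statistical analysis, Secondary endpoints:** define VAS at each time point as the mean of that time point's ratings, and use this value in the Friedman test and in the slow-wave-sleep regression. Name the week-4 time point the same way in both.

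Endpoint 4 then becomes a matched-night comparison, and it no longer matters which reading of the day labels was meant.

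**Cost:** with two baseline nights the count goes from 3 ratings to 2 + 2 + 2 = 6, so three more one-line ratings per patient. If both the pre-screening and the pre-Day 0 recordings in Fig. 1 count as baseline, it is 4 + 2 + 2 = 8, or five more. There is no extra visit and no change to the primary analysis. For patients already past baseline, the report should state which night each VAS rated.

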### Sample size calculation

This study is designed to demonstrate a statistically significant difference in the change from baseline in slow-wave sleep time in patients treated with desmopressin 50 μg with overall power of 80% and an overall Type 1 error rate of 5% (two-sided). The R program was used for sample size calculation. Bliwise et al. reported that in 15 patients studied, 8 patients had one or two voids, and 7 patients had three or four voids, showing a trend for higher amounts of N3 sleep at 81.4 ± 28.8 min vs 48.2 ± 40.7 min, respectively, assuming a total sleep time of 6 h [13]. Based on these data, we assumed 33.2 min as the difference between both groups and 35.7 min as the standard deviation, and determined that data from 13 subjects will be needed to detect a significant difference from baseline. Considering subject withdrawal, missing data, and feasibility, we assume 20 subjects will be sufficient.

### Statistical analysis

#### Primary endpoint

A Wilcoxon matched-pairs signed rank test would be used to compare the mean time of slow-wave sleep (N3 + N4) at Day 26 or 27 with that at baseline.

#### Secondary endpoints

A Wilcoxon matched-pairs signed rank test will be used to compare the mean score of the PSQI at Day 28 with that at baseline, and the mean time of slow-wave sleep (N3 + N4) at Day 5 or 6 with that at baseline. Friedman’s test and Dunn’s multiple comparisons test will be used to compare the change in mean total sleep time, mean sleep efficiency, mean sleep latency, mean VAS, mean time of sleep stages, and delta power during the FUSP from baseline to Day 26 or 27. The dependency between the mean time of slow-wave sleep (N3 + N4), the score of the PSQI, VAS, FUSP, number of voids, delta power during the FUSP, and other baseline characteristics will be analyzed using a linear regression model at Day 28. The significance level for statistical tests will be 0.05 on two sides.

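### The planned Day 28 regression of slow-wave sleep uses levels, not changes, so it cannot show that a longer FUSP goes with more slow-wave sleep within a patient; if fitted jointly, it is also too large for at most 20 patients

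*Protocol article*

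**What the plan says.** Table 1 of the protocol article lists as its fourth secondary endpoint: "Correlation between slow-wave sleep time (N3 + N4) and PSQI, VAS, FUSP, nocturnal urinay frequency at 28 days from baseline". The Secondary endpoints part of Statistical analysis gives the method. It begins "The dependency between the mean time of slow-wave sleep (N3 + N4), the score of the PSQI, VAS, FUSP, number of voids, delta power" and ends "delta power during the FUSP, and other baseline characteristics will be analyzed using a linear regression model at Day 28". That is slow-wave time plus five named variables, then an open set of baseline characteristics. Candidates for that set appear under Data collection: "Patient characteristics will include age, height, weight, and medical history".

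On numbers, the Informed consent and registration section states: "Registration will be closed when the planned total number of participants (20 participants) is reached". The Sample size calculation, made for the primary paired comparison only, says that "data from 13 subjects will be needed to detect a significant difference from baseline".

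The discussion paragraph of the abstract says the study will give evidence that desmopressin "prolongs the FUSP, resulting in the extension of slow-wave sleep time associated with sleep quality".

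The regression is the only method in the Statistical analysis section that uses FUSP length or number of voids. Every other mention of FUSP there concerns delta power. No stated analysis relates a change in FUSP or voids to a change in slow-wave time.

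**The concern.** There are two separate difficulties.

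The first is size. A single model with five or more covariates on 13 to 20 patients gives imprecise coefficients. A real FUSP association could easily be missed, and a sizeable R-squared would mean little.

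The second does not depend on how the covariates enter. The statement about FUSP and slow-wave sleep concerns what happens within a patient when treatment lengthens his first sleep period. A regression of Day 28 levels asks something else: whether men with a longer FUSP at Day 28 also have more slow-wave sleep at Day 28. Men who always sleep more deeply, and always wake later, would produce that pattern with no response to treatment at all. The risk is that a stable difference between patients is reported as support for the mechanism.

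**Working it through.** **The plan's own figure.** The stated 13 is for the primary test. With a difference of 33.2 min, SD 35.7 min, two-sided 0.05 and 80% power, a paired t-test needs n = 12 (power 83.4%). Dividing by the Wilcoxon efficiency, 12 / 0.955 = 12.57, so 13. Simulated signed-rank power is 79.3% at n = 12 and 84.4% at n = 13. The figure is reproduced, but the article gives no sample size or power for the regression.

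**Joint model.** Inputs: p = 5 named predictors if slow-wave time is the outcome; n = 20 (enrolment limit) and n = 13 (needed for the primary test). Adding three baseline characteristics, so p = 8, is an assumption. Residual df = n − p − 1. Expected R-squared with no association = p / (n − 1).

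| p | n | Patients per predictor | Residual df | Expected null R-squared |
|---|---|---|---|---|
| 5 | 20 | 4.0 | 14 | 5/19 = 0.26 |
| 5 | 13 | 2.6 | 7 | 5/12 = 0.42 |
| 8 | 20 | 2.5 | 11 | 8/19 = 0.42 |
| 8 | 13 | 1.6 | 4 | 8/12 = 0.67 |

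Simulated power for a standardised FUSP coefficient of 0.5 with residual variance 0.75. Both values are assumed, as is the pairwise correlation of predictors, ranging from 0 to 0.7:

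| Predictors | n = 20 | n = 13 |
|---|---|---|
| 1 | about 64% | about 43% |
| 5 | 54% down to 24% | 29% down to 14% |
| 8 | 44% down to 19% | 18% down to 9% |

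**Levels against change.** Suppose half the variance of both slow-wave time and FUSP is a shared stable trait, FUSP rises by the same amount in every man, and there is no within-patient link. The 50% is an assumption; the article gives no figure. In 5,000 simulated trials per sample size, the Day 28 level correlation reached p < 0.05 in 63% (n = 20) and 43% (n = 13). Change on change did so in about 5% at both sizes.

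To show the range: with trait share s the level correlation equals s, and the rejection rate is approximately Φ(atanh(s)·√(n − 3) − 1.96).

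- s = 0.25: Φ(0.255 × 4.123 − 1.96) = 18% at n = 20; Φ(0.255 × 3.162 − 1.96) = 12% at n = 13.
- s = 0.50: 62% and 41%, close to the simulation.
- s = 0.75: Φ(0.973 × 4.123 − 1.96) = 98% and Φ(0.973 × 3.162 − 1.96) = 87%.

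The 5% for change on change assumes that the night-to-night errors of the two measures are independent. If they are shared, it too would exceed 5%.

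**What one pair can deliver.** The Fisher interval for r = 0.5 is tanh(0.549 ± 1.96/√(n − 3)): 0.07 to 0.77 at n = 20 and −0.07 to 0.82 at n = 13. The correlation detectable with 80% power is about 0.60 and 0.71. These are Pearson figures, used here as a guide for Spearman.

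**Data available.** Table 3 schedules EEG and FVC before treatment and on Days 26 and 27, PSQI at Visit 2 and Day 28, and VAS at Day 0 and Day 28. Change can be formed for every variable in the proposed pairs.

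**The case against.** The sentence names no outcome and does not say that the variables enter together. Table 1 speaks of correlation, and the slope test in a simple regression is the Pearson correlation test. One regression per pair is therefore a fair reading, and it removes most of the overfitting. This stands, so the first difficulty is conditional. It does not touch the second.

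Table 1's reference to 28 days from baseline could mean change. The analysis sentence, however, says at Day 28, so levels is the better reading.

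Several stronger inferences are tempting, but the documents do not support them:

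- **FUSP and voids are near-duplicates, or delta power must dominate the model.** No correlation among these is given. One is the length of the first sleep period and the other a count over the night. Delta power is restricted to the FUSP, while slow-wave time is not. Overlap between delta power and slow-wave activity is enough reason not to adjust for it, but its size is unknown.
- **The null R-squared means false-positive coefficients.** Coefficient t-tests allow for residual degrees of freedom. The cost is imprecision and low power.
- **Table 1 and the analysis section contradict each other.** The added delta power and baseline characteristics go beyond the endpoint but do not conflict with it.
- **The whole mechanistic conclusion rests on this regression.** Change in slow-wave time and change in FUSP are endpoints in their own right. What is missing is an analysis linking the two.

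The study also calls itself exploratory and admits its small size and single open-label arm, which limits the weight of the point.

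**Conclusion.** The point holds in two parts of different strength. The firm part is that Day 28 levels in one treated arm cannot address a within-patient statement, however the predictors enter. With an assumed trait share of 50%, a purely between-patient association would be significant in 63% of trials at n = 20 and 43% at n = 13; the size moves strongly with that share.

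The conditional part is that a joint fit of five predictors leaves 14 (or 7) residual degrees of freedom, with expected null R-squared of 0.26 (or 0.42) and poor power for any one coefficient. Power figures and the eight-predictor case rest on assumed values.

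A reader might infer that switching to change scores would prove the pathway. It would not. Shared night-to-night variation can link the two changes, and the entry limit of 2.5 h on FUSP invites regression to the mean. The primary test is unaffected. This is a change that should be made to one secondary endpoint of an exploratory study.

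**What to change.** Replace the regression sentence as follows, with change taken from baseline to week 4:

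- Main association analyses: Spearman correlation, with 95% interval, of change in slow-wave time with change in FUSP, and with change in number of voids. One pair at a time.
- Next, in the same form: change in slow-wave time with change in PSQI and with change in VAS.
- No adjustment of these for delta power. Its own change stays as the separate endpoint already in Table 1.
- The Day 28 level correlations of Table 1, item 4, kept as descriptive.
- All labelled exploratory, with a statement that shared night-to-night variation and regression to the mean prevent a reading as treatment pathway.

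No new data or visits are needed. The change shifts the emphasis of secondary endpoint 4 from levels to changes, so Table 1 should be aligned and the change recorded before analysis. What is lost is mutually adjusted coefficients, which 13 to 20 patients could estimate only imprecisely. The intervals will still be wide: for r = 0.5, roughly 0.07 to 0.77 at n = 20.
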